### Measures

A schedule of assessments is provided in Table 1. Assessments are performed as close as possible to the allocated time-point. If the assessment cannot be performed within 6 weeks of the allocated time, this assessment is considered missed and the next assessment is performed at the allocated time.

**Table 1 Tab1:** Participant timeline

	Study period					
	Enrolment	Allocation	Post-allocation			Close-out
Timepoint	Baseline		Week 1–12	3 months	6 months	9 months
	(*t* _0_)					
Enrolment						
Eligibility screen	X					
Informed consent	X					
Allocation		X				
Interventions						
SMART			X			
Befriending			X			
Assessments						
QPR	X			X	X	X
Schizophrenia Hope Scale	X			X	X	X
UCLA Loneliness Scale	X			X	X	X
PANSS	X			X	X	X
SEPS	X			X	X	X
DASS-21	X			X	X	X
AQoL8D	X			X	X	X
STAR-Patient	X			X	X	X
Therapy Evaluation				X		
Serious Adverse Events	X		X	X	X	X
RUQ	X			X	X	X
ISMI	X			X	X	X
Self-efficacy measures	X			X	X	X
Demographics	X					
SCID	X					
Internet Use and Access	X			X	X	X
Recovery Style Questionnaire	X			X	X	X
Peer Identification Scale	X			X	X	X
Psychosis Attachment Measure	X			X	X	X
WTAR	X					
Cognitive tests	X					
Engagement measures			X	X	X	X
Medication and psychological treatment	X			X	X	X
Expectancy Scale			X			

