##### Recovery style

Recovery style refers to individual differences in adaptive coping during recovery from psychosis, which range from an *integrative* style in which the person approaches their psychotic experiences with curiosity and interest, to a *sealing over* style in which they are encapsulate their psychosis and see it as separate [70]. Past studies have suggested that persons with a sealing over style benefit less from interventions that involve discussion of mental health [71] making this a likely moderator of outcome. This will be measured using the Recovery Style Questionnaire, a self-report measure of 39 true/false items with good psychometric properties [72].

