##### Cognitive function

To determine whether cognitive function limits ability to benefit from resources, the WTAR will be used to control for premorbid IQ, in combination with tests of current cognitive functioning. The WTAR is administered as a test of premorbid IQ where participants are asked to read a list of 50 words that have atypical grapheme to phoneme translations (e.g., “liaison”, “ paradigm”) and are scored according to accuracy of pronunciation (raw score range 0–50). WTAR raw scores are standardised based on age then converted to the predicted WAIS-III IQ. While predicted IQ scores will be reported descriptively, these are associated with very large confidence intervals; standardised scores will therefore be used for analyses due to their greater precision. A small battery of cognitive functioning tests will additionally be administered. These include *Digit Symbol Coding* [76]*, Animal Fluency, Trails A and B* [76]*, Digits Forward and Digits Backward*. These tests assess the cognitive domains of executive function, verbal working memory, cognitive processing speed, task-switching and visual attention. Each assessment involves completion of paper and pencil cognitive assessments which are among the most frequently used in research and clinical practice and are well standardised with accepted norms. The battery takes a total of 8–10 min to complete. Each task will be briefly described below:

*Digit Symbol Coding* [75]*:* Participants are asked to use a key to write the numbers in a grid that correspond to nonsense symbols over a 90 s period. The total number of correct responses in used as the performance measure.

*Animal Fluency:* Participants are asked to give the names of as many animals as they can think of within a one-minute period. The number of unique animals produced is used as the primary performance measure, with repetitive errors or perseverations also noted.

*Trails A and B* [76]: For part A the participant is required to connect a series of 25 numbers in a circle as quickly as possible. They are asked to connect them in sequential order as quickly as possible without removing their pencil from the page. In part B the participant alternates between numbers and letters (i.e. 1, A, 2, B etc.). If the participant makes an error the experimenter corrects them before they move to the next circle. The time taken to complete each part is used as the performance metric.

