##### Intervention engagement/dose

Number of sessions attended and amount of time spent on each session will be recorded. In the SMART condition, access of the online materials using the participant’s username will be recorded automatically and usage within sessions and outside of sessions recorded.

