The differential effects on outcomes of the process variables (self-efficacy and self-stigma) and medication changes will be tested across conditions with a maximum likelihood Hierarchical Linear Modelling analysis. In these models time will be treated as a linear covariate. Baseline measures for cognitive function, recovery style, intervention engagement, diagnosis, demographics, baseline internet use and expectancy will be used as covariates, while testing interaction effects for condition and the baseline social engagement moderators (loneliness, attachment, peer group identification and peer contact). Structural equation modelling will then be used to demonstrate the mediation mechanism of outcome improvement for each condition separately, with bootstrap analyses used to obtain 95 % confidence intervals for all effect sizes.

Data will also be used as part of a broader economic evaluation of the use of the website involving cost-consequences analyses whereby incremental costs of interventions using the site are compared with the full spectrum of outcomes measured vs relevant comparators. For this study, QALYs will be calculated from AQoL8D data, and costs will be derived from estimates of the costs involved in running the website (website development and maintenance costs, forum moderation, and therapist activity data), adjusted for any differences in resource use between conditions. Standardised economic evaluation techniques will be used including incremental analysis of mean differences, with confidence intervals derived using bootstrapping.

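### Secondary process and moderator models adjust for engagement and expectancy as if they were baseline variables, although both are recorded after allocation; recovery style, named a likely moderator, gets no interaction test

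*Protocol article*

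**What the plan says.** The Data analysis section of the protocol article describes two layers of analysis. The primary one is a mixed model for repeated measures comparing change between arms, and no engagement or expectancy covariate is listed for it. The second is a set of hierarchical linear models for the process variables, medication changes and moderators. For these the article states: "Baseline measures for cognitive function, recovery style, intervention engagement, diagnosis, demographics, baseline internet use and expectancy will be used as covariates". The same sentence continues with "testing interaction effects for condition and the baseline social engagement moderators (loneliness, attachment, peer group identification and peer contact", so four variables are tested for interaction with condition.

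Four other places bear on this:

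- **Measures, Table 1.** The row "Engagement measures" is marked at weeks 1–12 and at 3, 6 and 9 months. The row "Expectancy Scale" is marked at weeks 1–12 only. Neither has a mark under baseline or allocation.
- **Intervention engagement/dose.** "Number of sessions attended and amount of time spent on each session will be recorded", and "In the SMART condition, access of the online materials using the participant’s username will be recorded automatically".
- **Recovery style.** The article gives a reason why people with a sealing-over style may gain less from interventions that discuss mental health, "making this a likely moderator of outcome".
- **Cognitive function.** The tests are given "To determine whether cognitive function limits ability to benefit from resources". The section then says that the summary score will be used as a covariate.

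**The concern.** A covariate measured before randomisation cannot be changed by the allocated arm, so adjusting for it leaves the comparison between arms intact. A variable measured after allocation has no such protection. If the arm shifts it, adjustment removes whatever part of the effect runs through it. If it also shares unmeasured causes with the outcome (motivation or illness severity, for example), adjustment brings in confounding that randomisation had removed. Both problems reach the condition-by-moderator terms as well as the condition term.

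The interpretation of these secondary models is at stake. They serve a stated aim, since the Aims section includes examining mechanisms of change. The recovery-style problem is of another kind: a main-effect covariate shows whether style predicts outcome in both arms together. It cannot show whether one style benefits less from SMART than from Befriending.

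**Working it through.** The plan gives no figure on this point to reproduce. Its sample size of 148 does not enter the argument.

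**Step 1: timing.** In Table 1 the SMART and Befriending rows each carry one mark, in the weeks 1–12 column. The single Expectancy Scale mark and the first engagement mark stand in that same column, after the allocation column. So 2 of the 7 listed covariates have no baseline value. The sentence repeats the word baseline before internet use, so it could be read as applying that label to only some items. On that reading the label is no longer wrong, but two post-allocation variables are still adjusted for.

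**Step 2: can allocation affect them?** Attendance and session time are part of the treatment received. Website use is recorded for SMART only and has no Befriending counterpart, so as a covariate it would be tied to condition. The Allocation and blinding section says that participants know their condition and that the trial's framing was chosen to limit expectancy effects. Expectancy rated in weeks 1–12 can therefore respond to the arm.

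**Step 3: what adjustment does.** Take a single-outcome model with condition T coded ±0.5, a baseline moderator M, an unmeasured cause U, and a post-allocation variable E with residual variance 1:

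- E = a·T + m·T·M + g·U + noise
- Y = 0.30·T + 0.20·T·M + b·E + g·U + noise

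Without E in the model, the condition coefficient is 0.30 + a·b and the interaction is 0.20 + m·b. With E in the model, its own coefficient becomes b + g², the condition coefficient becomes 0.30 − a·g², and the interaction becomes 0.20 − m·g². Adjustment thus moves the two terms by −a·(b + g²) and −m·(b + g²). Every input here is an assumption. A simulation with 400,000 subjects agrees with the formulas.

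| a, m, b, g | Condition: unadjusted → adjusted | Interaction: unadjusted → adjusted | Simulated (condition; interaction) |
|---|---|---|---|
| 0, 0, 0.3, 0.5 | 0.30 → 0.30 | 0.20 → 0.20 | 0.296 → 0.297; 0.196 → 0.193 |
| 0.3, 0.3, 0, 0.5 | 0.30 → 0.225 | 0.20 → 0.125 | 0.299 → 0.223; 0.202 → 0.125 |
| 0.3, 0.3, 0.3, 0 | 0.39 → 0.30 | 0.29 → 0.20 | 0.390 → 0.299; 0.290 → 0.199 |
| 0.3, 0.3, 0.3, 0.5 | 0.39 → 0.225 | 0.29 → 0.125 | 0.385 → 0.222; 0.288 → 0.125 |
| 0.5, 0.5, 0.5, 0.5 | 0.55 → 0.175 | 0.45 → 0.075 | 0.548 → 0.173; 0.455 → 0.078 |
| −0.3, −0.3, 0.3, 0.5 | 0.21 → 0.375 | 0.11 → 0.275 | formula only |

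In the first row allocation does not touch E, and adjustment does no harm. In the second, E has no effect on outcome at all, yet the shared cause alone biases both terms. In the last, allocation lowers E and the adjusted terms come out larger.

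**Step 4: moderators.** Set the Measures text beside the analysis text:

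- Attachment is described as a potential moderator and does receive an interaction with condition.
- Recovery style is described as a likely moderator and receives none.
- Cognitive function is never called a moderator, and the Cognitive function and Data analysis sections agree that it is a covariate. Only its stated purpose reads like a moderation question.

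**The case against.** The strongest reply is that little depends on this. The trial's effect is estimated by the primary mixed model, which uses none of these covariates. That is correct, and it settles the severity. A reader might infer that the primary treatment estimate is biased; the document does not support that.

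Next, both arms are offered eight 50-minute sessions by the same workers, so attendance might not differ by arm. This is possible, and the first row of the table shows that adjustment would then be harmless. But the plan cannot rely on it in advance, and it does not cover website use or expectancy.

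Third, models containing self-efficacy, self-stigma and medication change are not pure randomised comparisons anyway. This also stands, and it narrows the point to models whose condition or condition-by-moderator terms will be interpreted. It does not follow that medication change should be dropped: it is not in this covariate list, and the article studies it in order to see whether other treatment accounts for outcomes.

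Fourth, the article does not describe how the Expectancy Scale is given. Its timing rests on one table cell. That cell lies after allocation, and nothing in the text contradicts it.

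Finally, a reader might infer that two named moderators were reduced to covariates. Only recovery style was. A reader might also want an instrumental-variable analysis of dose. That is not a simple substitute here, because Befriending is itself an eight-session contact, which makes the exclusion restriction doubtful. The Befriending section already foresees secondary analyses using a four-session threshold.

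**Conclusion.** The point holds for the secondary process and moderator models only, as a should-fix. As written, the plan adjusts for two variables that are not baseline measures and that allocation can change. The resulting bias may go in either direction. Its size cannot be known from the document, because it depends on how far allocation shifts engagement and expectancy, on their effect on outcome, and on shared unmeasured causes. The tabulated values are illustrations, not forecasts. They also simplify the planned models, in which time is a linear covariate. If the covariates enter as main effects only, a condition-by-time slope would be largely spared, and the damage would fall on the condition and condition-by-moderator terms. The recovery-style mismatch needs no assumption: the article raises a moderation question and lists no test that could answer it.

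**What to change.** - Remove intervention engagement and expectancy from the covariate set of every model used to interpret condition or condition-by-moderator effects, and keep only variables measured at t0.
- Report engagement and expectancy by arm, labelled as post-randomisation variables. Report website use as a SMART-only description.
- Add a condition-by-recovery-style interaction, using the baseline score, to the exploratory moderator tests.
- Optionally, add condition by cognition, but only if the question of whether cognition limits benefit is to be answered. Otherwise, reword that stated purpose to match its use as a covariate.

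The cost is analysis wording. No new data are needed and the sample size does not change. The downside is one or two more exploratory interaction tests in a trial sized for a main effect of d = 0.5, so they should be reported as exploratory, with confidence intervals.

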**Methods/Design:**

This is a rater-blinded randomised controlled trial comparing a low intensity recovery intervention of eight one-to-one face-to-face sessions with a mental health worker using the SMART website alongside routine care, versus an eight-session comparison condition, befriending. The recruitment target is 148 participants with a schizophrenia-related disorder or mood disorder with a history of psychosis, recruited from mental health services in Victoria, Australia. Following baseline assessment, participants are randomised to intervention, and complete follow up assessments at 3, 6 and 9 months post-baseline. The primary outcome is personal recovery measured using the Process of Recovery Questionnaire (QPR). Secondary outcomes include positive and negative symptoms assessed with the Positive and Negative Syndrome Scale, subjective experiences of psychosis, emotional symptoms, quality of life and resource use. Mechanisms of change via effects on self-stigma and self-efficacy will be examined.

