## Methods/Design

### Aims

This study (acronym SMART-Therapy) is part of a broader research program (Self-Management and Recovery Technology) developing and trialling digital resources for specialist mental health services. It is a randomised controlled trial of a discrete psychosocial intervention to promote personal recovery in people with persisting psychosis. The intervention adopts a low intensity delivery model blending a course of individual face-to-face sessions with use of a website featuring lived experience content on recovery. The primary objective is to determine if this intervention will be superior to a time-equivalent comparison intervention that incorporates exploration of non-recovery-related digital resources on a measure of consumer-defined personal recovery. We will also examine a number of secondary outcomes, interview people about their experience of the intervention, use data as part of a broader economic evaluation, and examine mechanisms of change.

In examining the mechanisms of the intervention, we hypothesise effects on personal recovery via two measurable processes: (a) mental illness self-stigma and (b) self-efficacy for mental health recovery. Self-stigma, also referred to as internalised stigma, refers to the extent to which an individual adopts negative community stereotypes about mental illness and the extent to which these exert an influence on experience and behaviour [43]. For persons with persisting psychosis, these may include stereotypes of being fundamentally different from others, of inherent dangerousness, of pessimistic long-term outcomes, and of being insufficiently capable of fulfilling social roles such as parenting and work [44]. Internalised stigma includes components such as negative stereotype endorsement, alienation and social withdrawal [45]. In studies of public stigma, contact with persons with mental illness that undermines negative stereotypes and humanises persons with a mental illness appears effective in reducing negative stereotypes [46]. We hypothesise that positive portrayal of peers may have a parallel effect on internalised stigma [41].

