### Design

The SMART-Therapy trial is designed as a randomised, controlled, assessor-blinded superiority trial, with two parallel groups, using a 1:1 allocation ratio. The two groups both receive eight sessions with a mental health worker in addition to their routine care during a three month window, with one group being delivered the recovery intervention, and the other being delivered a befriending intervention as a comparison condition. Outcome measures are completed at baseline (prior to randomisation) and are repeated at 3, 6 and 9 months following baseline.

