### Participants

The study is being conducted across multiple public community mental health services in the state of Victoria, Australia, including clinical mental health services, and not-for-profit organisation-run community mental health support services. Potential participants are identified via referral from practitioners in collaborating services, supplemented by review of case-lists, plus advertising within services, and in print and online social media.

Inclusion criteria are: (a) age between 18 and 65 years inclusive; (b) diagnosis of a nonorganic psychotic disorder (schizophrenia-related disorder or bipolar disorder or major depressive disorder with psychotic features present within the past 2 years), confirmed using the Structured Clinical Interview for DSM-IV-TR Axis I Disorders (SCID) [49]; (c) sufficient conversational English for meaningful participation; (d) overall intellectual functioning within normal limits (having an IQ greater than 70, as estimated by the Wechsler Test of Adult Reading (WTAR) [50]) to ensure they have the cognitive capacity to provide consent, in addition to being able to adequately engage with the intervention. Exclusion criteria are: (e) initiation of a new antipsychotic medication, or commencement or completion of a formal psychological treatment, within the previous 8 weeks; (f) inpatient admission within the previous 8 weeks.

The recruitment target is 148 participants, providing 80 % power to detect medium effect sizes (*d* = 0.5) at α = .05 with 15 % attrition. This was based on an average effect size of *d* = 0.53 observed in a meta-analysis of online interventions [51].

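### The mediation SEM, fitted within each condition separately, does not estimate the between-arm indirect effect that the mechanism hypothesis is about

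*Protocol article*

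**What the plan says.** The Aims section sets out the mechanism as a claim about the intervention: "In examining the mechanisms of the intervention, we hypothesise effects on personal recovery via two measurable processes". The two processes are self-stigma and self-efficacy for recovery. The abstract repeats the aim: "Mechanisms of change via effects on self-stigma and self-efficacy will be examined".

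The Data analysis section gives two analyses of the process variables:

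- A hierarchical linear model: "The differential effects on outcomes of the process variables (self-efficacy and self-stigma) and medication changes will be tested across conditions".
- The mediation analysis proper: "Structural equation modelling will then be used to demonstrate the mediation mechanism of outcome improvement for each condition separately". Its 95% confidence intervals are to come from bootstrapping.

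The mixed-model repeated-measures analysis earlier in that section compares the arms over the follow-up period. ISMI and the self-efficacy items appear under a separate Process variables heading, and the section states no between-arm analysis of them by name. It also describes no contrast between the two per-condition SEMs.

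**The concern.** The hypothesised mechanism is a product of two paths: the effect of being allocated SMART rather than Befriending on the mediator, and the effect of the mediator on QPR. Only the first path is protected by randomisation. Splitting the data by condition removes it.

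What remains within an arm is the association between mediator and outcome, and possibly the average change over time. Neither is specific to SMART. All three instruments are self-reports, so some association is to be expected in either arm. Improvement over time can come from contact with a worker, regression to the mean or usual care. Befriending was chosen to control for worker time and technology use, and a SMART-only model does not use that control.

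The risk is that a mediator-outcome association, or improvement common to both arms, is reported as SMART's mechanism. The Discussion says the mechanism results are meant to inform use of this intervention and of peer support more widely, so the attribution matters.

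**Working it through.** **1. Inputs from the article.** Design: "with two parallel groups, using a 1:1 allocation ratio". Sample size (Participants): "The recruitment target is 148 participants, providing 80 % power to detect medium effect sizes", with d = 0.5, α = .05 and 15% attrition. Sidedness is not stated; two-sided is assumed.

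**2. The plan's own figure.** The normal approximation gives n per arm = 2(1.96 + 0.84)²/0.5² ≈ 63, so 126 in total, and 126/0.85 = 148.2. The t-test version gives 64 per arm, and 128/0.85 = 150.6. Both are within 3% of the stated 148, so the target reproduces. After 15% attrition, 148 × 0.85 = 125.8, or about 63 analysed per arm. The article gives no figure for the mediation analysis itself.

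**3. What each model can estimate.** Let A be arm (0 or 1), M the change in mediator and Y the change in outcome:

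- M = μ + a·A + error
- Y = b·M + c·A + error

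The hypothesised indirect effect is a·b.

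| Analysis | Estimates a? | Estimates b? | Estimates a·b? |
|---|---|---|---|
| SEM within one condition (A constant) | no | yes, in that arm | no |
| HLM across conditions | no | difference in b between arms | no |
| MMRM on outcomes | no | no | no (total effect only) |
| One model with A as exposure | yes | yes | yes |

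If change over time is treated as the first path within an arm, the product is μ·b in Befriending and (μ + a)·b in SMART. The part due to SMART is the difference between them, a·b when the slopes are equal, and the article describes no such difference.

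**4. Illustration.** These values are assumptions, not taken from the article: one mediator, error SD 1, b = 0.5, c = 0, 63 per arm, 4,000 simulated trials, and a Monte Carlo interval for the product in place of the bootstrap.

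With a shared improvement of μ = 0.5 SD:

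| True arm effect on mediator | True a·b | SMART-only product (μ + a)·b | SMART-only interval excludes 0 | Joint-model interval excludes 0 | Condition × mediator test rejects |
|---|---|---|---|---|---|
| a = 0 | 0 × 0.5 = 0 | 0.5 × 0.5 = 0.25 | 94% | 6% | 5.4% |
| a = 0.5 | 0.5 × 0.5 = 0.25 | 1.0 × 0.5 = 0.50 | 97% | 81% | 4.9% |

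The mediator-outcome path within SMART is significant in 96% of trials in both rows. The condition × mediator test rejects at about its nominal rate in both rows because the slopes were set equal. It carries no information about a.

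**5. Sensitivity to the shared improvement (a = 0).** The SMART-only product interval excludes zero in about 94% of trials at μ = 0.5 SD, about 34% at 0.2 SD and about 6% at zero. The size of the problem for the product therefore depends on how much both arms improve, which the article does not give.

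**The case against.** **Condition is not absent from the process analyses.** The HLM uses it, and the SEM follows the HLM. This is right. However, a difference in mediator-outcome slope between arms is moderation. It tests neither the arm-to-mediator path nor the indirect effect.

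**The MMRM may cover the mediators.** Its wording is not expressly limited to named outcomes, and ISMI and self-efficacy are collected at baseline, 3, 6 and 9 months. On that reading the arm-to-mediator path would be tested. The reading is possible but unconfirmed, and it would still give no indirect effect or interval.

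**The phrase may condense a multi-group SEM.** Comparing mediator intercepts across groups would recover the missing path. The article says the conditions are handled separately and mentions no cross-group contrast. If one is intended, stating it would resolve the point.

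**The within-arm model is not empty.** Change over time, sessions attended and website use all vary within an arm. These are not randomised contrasts, so they answer a weaker question.

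A reader might also infer more than the documents support:

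- *That the mechanism cannot be tested at all.* The data allow it; the stated model does not do it.
- *That the plan would report mediation whenever SMART does nothing to the mediators.* For the product, this depends on substantial improvement shared by both arms, as the sensitivity figures show.
- *That halving the sample costs a fixed amount of precision.* A loss by a factor of √2 in the standard error of the mediator-outcome path holds only if that slope is equal in both arms.
- *That shared self-report bias separates the two approaches.* It also affects the mediator-outcome path of a joint model.

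**Conclusion.** The point holds in limited form. As worded, the SEM does not estimate the SMART-versus-Befriending indirect effect that the abstract and Aims hypothesise, and no other stated analysis supplies it. Mediation within an arm cannot be attributed to SMART over Befriending.

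The structural conclusion needs no assumed effect sizes. The size of the risk does: the range from about 94% down to about 6% rests on the assumed slope, the assumed shared improvement and 63 analysed per arm.

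This should be fixed, but it is not critical to the trial. Mechanisms are a secondary aim, and a reader should not infer that the primary QPR comparison, the sample size, the randomisation or the data collection is affected.

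**What to change.** Replace the per-condition SEM as the mediation analysis with one SEM on all randomised participants, with condition as the exposure. A multi-group SEM with an explicit cross-group contrast would also serve. Report the indirect effect with the bootstrap 95% confidence interval already planned.

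Preferably use the 3-month mediators and later QPR (6 or 9 months), so that the mediator precedes the outcome, and adjust for baseline mediator and baseline QPR. Allow a condition × mediator term. These refinements are good practice; the essential change is to bring condition into the model. Keep the per-arm models as a description of the mediator-outcome association only.

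The cost is analysis wording. The participant timeline table already schedules QPR, ISMI and the self-efficacy measures at baseline, 3, 6 and 9 months.

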##### Quality of life

Quality of life will be measured using the Assessment of Quality of Life (AQoL)-8D [65] consisting of 35 items across eight dimensions comprisingphysical (independent living, pain, senses) and psychosocial (mental health, happiness, coping, relationships, self-worth) dimensions of quality of life. The AQoL-8D is comprehensively validated and demonstrates high test-retest reliability [66]. The AQoL-8D total and physical and psychosocial scores will be used as a secondary outcome, and the utility scoring algorithm will be used to derive quality adjusted life years (QALYs) for an economic analysis which will integrate these data with those from other studies in the research program and be reported upon separately.

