##### Service use

Although differences in service use are not formally hypothesised as an outcome of the intervention, a resource use questionnaire (RUQ) is administered in order to assess for any differences in mental health service utilisation between the groups before, during, and following intervention. This will be used to derive costings for the economic analysis. The RUQ was modified for the local context of the study, assessing use of mental health services in Victoria including hospital admissions (number and days) and consultations with mental health service providers (number and length). This will be supplemented by Australian Government Medicare data: these administrative data are complete, but do not include the full spectrum of services which participants in this study are likely to use.

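### The incremental QALY comparison gives no role to the baseline AQoL-8D utility the trial collects; stating a baseline-adjusted estimate would tighten the interval at almost no cost

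*Protocol article*

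**What the plan says.** The economic paragraph of the Data analysis section fixes the source of the outcome, "For this study, QALYs will be calculated from AQoL8D data", and names the comparison: "Standardised economic evaluation techniques will be used including incremental analysis of mean differences, with confidence intervals derived using bootstrapping". The Quality of life section agrees on the source: "the utility scoring algorithm will be used to derive quality adjusted life years (QALYs) for an economic analysis". It adds that this analysis will be combined with data from other studies in the programme and reported separately.

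On timing, the Design section says: "Outcome measures are completed at baseline (prior to randomisation) and are repeated at 3, 6 and 9 months following baseline". Table 1 schedules both the AQoL-8D and the resource use questionnaire (RUQ) at all four points, and the Service use section says the RUQ is there to "assess for any differences in mental health service utilisation between the groups before, during, and following intervention".

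The process and moderator models in the Data analysis section come with a list of baseline covariates. The economic paragraph lists none for QALYs. For costs it mentions an adjustment for resource-use differences between the arms, without saying how it is made or whether baseline use enters it.

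**The concern.** A QALY is a single number per participant, built from the utility curve over time. If the curve starts at baseline, as is usual, the pre-randomisation utility is part of the outcome and also predicts the later utilities. A plain difference in mean QALYs therefore counts some of any chance baseline difference between arms as QALYs gained or lost, and a bootstrap of that difference does not remove it.

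The mixed model used for the clinical outcomes does not help, because a one-value-per-person QALY has no time term or change contrast. Minimisation is on service type, PANSS total in two levels and Internet use, so it balances utility only indirectly.

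At stake are the precision of the QALY increment and its exposure to an unlucky draw. There is also a smaller matter of prespecification: if the article is all there is, the choice to adjust could be made after the imbalance has been seen.

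**Working it through.** **Sample size first.** The Participants section states: "The recruitment target is 148 participants, providing 80 % power to detect medium effect sizes" (d = 0.5) "at α = .05 with 15 % attrition", and the Design section states allocation "using a 1:1 allocation ratio". Taking a two-sided test (sidedness is not stated), the normal formula gives 63 per arm, and 126/0.85 = 148.2. With the t distribution it is 64 per arm, and 128 × 1.15 = 147.2, rounded up to 148. The figure of 148 reproduces. After 15% attrition, 148 × 0.85 / 2 ≈ 63 per arm are analysed. The article states no precision or power figure for the economic comparison.

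**Assumptions not in the article.** Trapezoid QALY; equal utility variance at each visit; between-visit correlation r of 0.3 to 0.7, either equal for all pairs or first-order autoregressive; 63 per arm. Utilities are in SD units.

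**Weights.** With visits at 0, 0.25, 0.5 and 0.75 years, QALY = 0.125·U0 + 0.25·U3 + 0.25·U6 + 0.125·U9. The weights sum to 0.75, so baseline carries 0.125/0.75 = 1/6.

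**Formulas for equal correlation.**
- Slope of QALY on baseline utility: c = 0.125 + 0.625r
- Variance of QALY: v = 0.5625r + 0.15625(1 − r)
- Share of QALY variance explained by baseline: R² = c²/v
- Interval width, adjusted over unadjusted: √(1 − R²)

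At r = 0.5: c = 0.4375; v = 0.28125 + 0.07813 = 0.3594; R² = 0.1914/0.3594 = 0.533; width ratio √0.467 = 0.684.

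**Autoregressive case.** c = 0.125 + 0.25r + 0.25r² + 0.125r³ and v = 0.15625 + 2(0.125r + 0.0625r² + 0.015625r³). At r = 0.3: c = 0.2259; v = 0.2433; R² = 0.0510/0.2433 = 0.21; width ratio √0.79 = 0.889.

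| Correlation | r | R² | Width ratio | Narrower by |
|---|---|---|---|---|
| Equal | 0.3 | 0.35 | 0.806 | 19% |
| Equal | 0.5 | 0.53 | 0.684 | 32% |
| Equal | 0.7 | 0.72 | 0.531 | 47% |
| Autoregressive | 0.3 | 0.21 | 0.889 | 11% |
| Autoregressive | 0.5 | 0.34 | 0.812 | 19% |
| Autoregressive | 0.7 | 0.54 | 0.680 | 32% |

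**Carry-over of a chance imbalance (equal correlation 0.5).** A 0.2 SD baseline difference shifts the unadjusted QALY difference by 0.4375 × 0.2 = 0.0875 utility-SD-years with no treatment effect. The standard error of that difference is √0.3594 × √(2/63) = 0.599 × 0.178 = 0.107, so the shift is about 0.8 of a standard error. Only 0.125 × 0.2 = 0.025 (about 0.23 of a standard error) comes from the baseline weight itself; the rest comes through the assumed correlation with later visits.

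**Does the propensity rule cover this?** The Data analysis section adds a propensity-score covariate when outcome measures show significant baseline differences. With 63 per arm, two-sided 5% significance needs about 1.96 × 0.178 = 0.35 SD. Under simple randomisation, P(|imbalance| > 0.2 SD) = 2(1 − Φ(0.2/0.178)) ≈ 0.26, and 0.05 reach significance. In about 0.26 − 0.05 = 0.21 of trials, then, utility would be out of balance by 0.2 to 0.35 SD without triggering the rule. Minimisation may lower these probabilities to the extent that its factors relate to utility.

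**The case against.** The strongest objection is that the article never says the comparison is unadjusted. The list of techniques is open-ended, and a regression-adjusted, bootstrapped increment is also an incremental mean difference. The economic analysis belongs to a wider evaluation reported elsewhere, and a journal article may well leave its covariates to a fuller plan. This stands in part: adjustment is neither stated nor excluded, and that keeps the severity low. It does not dispose of the point, because the article does name an estimator and an interval for this study's QALYs and leaves the collected baseline utility out of both.

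The propensity rule is a partial answer at best. It depends on significance, it is not said to extend to QALYs, and it gives no routine gain in precision.

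There are stronger readings that a reader might infer and that the documents do not support:

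- **Bias or a reversed conclusion.** Randomisation keeps the unadjusted difference unbiased on average. A change of sign would need both an unlucky draw and a small true increment.
- **A matching flaw in costs.** The named costs of building and running the site, moderating its forum and worker time have no pre-randomisation counterpart. Only the service-use component has a baseline value, and no size can be put on it from the article.
- **A stated loss of power.** The article plans a cost-consequences analysis with intervals and no test of QALYs, so a power figure would describe an analysis it does not propose.
- **Exact imbalance probabilities.** The 26% figure assumes simple randomisation; the trial uses minimisation.

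**Conclusion.** The point holds as a low-severity improvement. Read plainly, the plan compares mean QALYs without adjusting for a baseline utility it already collects. This leaves chance imbalance in the increment and widens the interval. The gain from adjustment is about 11% to 47% in interval width, resting on the trapezoid rule, equal variances and correlations of 0.3 to 0.7. The direction holds for any positive correlation; the size depends on figures the article does not give. The analysis is secondary and separately reported, and neither the primary QPR analysis nor the recruitment target is affected.

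**What to change.** In the economic paragraph of the Data analysis section, state that incremental QALYs will be estimated by regressing each participant's QALY on arm, baseline AQoL-8D utility and the three minimisation factors. State also that bootstrap intervals will resample participants with cost and QALY kept together, refitting the regression each time. Keep unadjusted means by arm as a descriptive row. For costs, baseline RUQ use may be a covariate for the service-use component only.

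The cost is a sentence or two of wording and a few extra covariates, with no new data. The one drawback is that the adjusted increment will not equal the difference between the tabulated means, which a footnote can explain. If a fuller economic plan already specifies this, a reference to it is enough.
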